## 4. Expected Results

A reduction in the incidence of pregnancy among the participants, behavioral change, utilization of services and increased awareness on sexual and reproductive health.

## 5. Discussion

This study will address central gaps in the evidence base in regard to the prevention of adolescent pregnancy among the school girls. To our knowledge, this is the first CRCT to be conducted in Uganda focusing on adolescent girls in schools and employing combination intervention using the three tire approach. The results of the study will effectively inform programming.

## Figures and Tables

**Figure 1 mps-02-00021-f001:**
[figure not shown]
Flow chart on the Sampling framework. Source: Primary data 2018.

**Table 1 mps-02-00021-t001:** Categorization of study respondents. ASRH: Adolescent Sexual and Reproductive Health.

	Category of Respondent	Sample Size	Data Collection Tool
1	Adolescent girls (15–19 years) in school	1080	Questionnaire
2	Adolescent girl (15–19 years) who dropped out of school due to pregnancy related reasons	2	Key Informant Interview guide
3	ASRH Health workers	1	Key Informant Interview guide
4	Local council leader (chairperson)	1	Key Informant Interview guide
5	Community leaders	10	Focus Group Discussion guide
6	District leaders (Chief Administrative Officer, District Health Officer, District Education Officer)	3	Key Informant Interview guide
7	School heads	1	Key Informant Interview guide
8	School Matron	1	Key Informant Interview guide
9	Parents to adolescent girls in school	15	Focus Group Discussion guide
10	Adolescent boys (15–19 years) in school	15	Focus Group Discussion guide
11	Teachers	10	Focus Group Discussion guide
12	Domestic workers/axillary staff at school	10	Focus Group Discussion guide

Source: Primary data, 2018.

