Adolescent pregnancy and motherhood has detrimental socioeconomic and psychological outcomes for the young mother, her child, and her young siblings. When a girl becomes pregnant, her education may end, her job prospects diminish, she becomes more vulnerable to poverty, her health often suffers and the complications from pregnancy and childbirth are the leading cause of death among adolescent girls. The child on the other hand is likely to live in poverty, grow up without a father, become a victim of neglect or abuse, do less well at school, become involved in crime, abuse drugs and alcohol, eventually become a teenage parent themself and begin the cycle all over again [2,3].

The consequences of adolescent pregnancy include premature births, low birth weight of the newborn, high risks for medical complications such as obstructed labor, obstetric fistula, leakage of urine and/or feces and mortality [9]. Adolescent girls account for 14% of the estimated 20 million unsafe abortions performed each year, which result in approximately 68,000 deaths. This is an alarming public health problem globally and requires urgent multi-sectoral attention [9].

In 2013, there were nearly 300,000 abortions in Uganda, which is equivalent to 54 abortions per 1000 women of reproductive age, or one abortion for every 19 such women. This rate is far higher than the average rate for Eastern Africa, which is 36 abortions per 1000 women [17]. In addition, the Ministry of Health in Uganda estimated that abortions accounted for 26% of maternal mortality in 2008; this is higher than the 18% in the Eastern African region and the 13% in the world as a whole [1,17]. The Uganda Demographic Health Survey (UDHS), conducted in 2016, estimated the pregnancy-related mortality ratio to be at 368 death per 100,000 live births and adolescents 15–19 years contributing 17% of all pregnancy related mortality rate in Uganda. Additionally, 15 out of every 1000 Ugandan women of reproductive age were treated for abortion complications that year [4]. Therefore, it is paramount to pay special attention to adolescents to prevent maternal mortality due to unsafe abortions among the adolescents.

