#### 2.1.2. Dependent Variable: Prevention of adolescent pregnancy

Primary outcomes
(a)Incidence of pregnancy(b)Sexual and Behavior change(c)Utilization of SRH services

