*^n^*_Cluster_Binary_ = *^n^*_Individual_Binary_ × [1+ (*m* − 1) *ρ*] = 282.5 × [1 + (60 − 1) × 0.01] = 449 adolescent girls per group = 449 × 2 = 898 individuals for the entire study (449 per group)

The final total sample size (898) will be increased by 10% to 988 participants to cater for a non-response insurance factor of 10%. Therefore, the treatment and control group will each have 494 adolescent girls.

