### 2.6. Sampling Techniques

The study will use multi-stage sampling technique to select the study population. The Hoima District was purposively selected because of the high (29%) adolescent pregnancy and the thriving economic activities, which further increase the vulnerability of the adolescent girls to pregnant. The District has 36 registered secondary schools in four constituencies Kigorobya, Bugahya, the Hoima municipality and the Buhaguzi counties.

**Cluster Sampling:** Clusters of adolescent girls attending secondary school who represent the target population will be identified and included in the sample [34]. This will be used to increase the level of efficiency of sampling and each cluster will be considered as a sampling unit. In this study, the clusters will be secondary schools registered and operational in the Hoima District; a list of all clusters (schools) will be generated from the District Education Office and clusters will be ranked according to the level of school dropout rate. The top 18 clusters (schools) with the highest dropout rate will be considered for the study. The selection will be based on the judgment of the researcher using drop-out rates at each school within the population in the Hoima District. The schools to be selected from each county should rank highest in dropout rates of adolescent girls in the last 12 months prior to the study. Four to five secondary schools with the highest student enrolment and highest school dropout rates will be selected from each county. The statistics will be derived using the annual school dropout reports from the Hoima District Education Officer (DEO) and the Chief Administrative Officer (CAO). In addition to the school dropout rates, the schools to participate in the study will meet the following requirements:Permission to conduct outreach SRH services at school and willingness of the head teacherAvailability of SRH focal person usually called the ‘senior woman teacher’Proximity to a functional public health center (within 5–10 km)Access to eligible studentsGeographical location of the school

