#### 2.8.3. Tier Three: Referrals to off-Site Public Health Facilities

The students identified in need of advanced ASRH care such as post abortion care, antenatal care and HIV treatment will be referred to primary or tertiary public health facilities for further management. Details of the reasons for referral will be recorded and a Ministry of Health (MOH) referral form filled and given to the student. The health workers at the public health facilities nearest to the school will be sensitized about the study and possible referrals to be made and a mechanism of management of the referred cases will be developed to prevent delays and stigma associated with adolescent SRH care. The district ASRH officer will take lead in this activity for ownership but also to monitor the response of health workers during the implementation.

**Follow-up:** Follow-up of the participants will be done for 12 months and data will be collected at the start of the study, after six completed months and at the end of the study after 12 months. Data on student demographics, services received and perception towards the service and provider will collected on each clinic day to assess the level of utilization and the most sought after services.

**Control Group**: The clusters in this arm will not receive any intervention from the research team. However, the participants are free to continue accessing services from the nearby facilities as has been the case prior to the study.

**Data Collection Methods:** Quantitative data will be collected using the survey method three times that is at the start of the study (0 months), six months and at the end of the study after 12 months. Qualitative data will be collected once during the 12 months of the study through interviews and discussions with the identified stakeholders. This is intended to provide subjective and relevant information to enrich the quantitative data on adolescent pregnancy in the Hoima District.

**Data Collection Tools:** Quantitative data will be collected using a self-administered questionnaire while Qualitative data will be collected using the Key Informant Interview guide and discussions using the Focus Group Discussion guides. Additional qualitative data will be collected at other SRH service delivery point to provide a snapshot on the level of utilization of services provided; this will be done using an SRH utilization register.

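### No route is given to the pregnancy outcome of enrolled girls who leave school, although pregnancy is itself a reason to leave, so a selective share of primary events is at high risk of being missing

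*Protocol article*

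**What the plan says.** - **Outcome.** Section 2.1.2 lists "Incidence of pregnancy" first among the primary outcomes. The sample size in Section 2.4 rests on the proportion pregnant.
- **Tool.** Under Data Collection Tools (Section 2.8.3): "Quantitative data will be collected using a self-administered questionnaire". The survey is run at 0, 6 and 12 months. The service register is there to describe utilization.
- **Respondents.** Table 1 gives the questionnaire to 1080 "Adolescent girls (15–19 years) in school". A separate row, "Adolescent girl (15–19 years) who dropped out of school due to pregnancy related reasons", has a sample size of 2 and the key informant interview guide.
- **Pregnancy and schooling.** The Introduction states: "When a girl becomes pregnant, her education may end".
- **School selection.** Section 2.6: "The top 18 clusters (schools) with the highest dropout rate will be considered for the study". Within each county the schools "should rank highest in dropout rates of adolescent girls in the last 12 months prior to the study". Neither the dropout rate nor its causes are given.
- **Loss.** Section 2.4.2 raises the total from 898 to 988 to "cater for a non-response insurance factor of 10" per cent.
- **Commitments.** Section 2 and Section 3 promise an intention-to-treat analysis, and Section 2.8.3 promises 12 months of follow-up. Neither says how a girl who has left school would be reached.

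**The concern.** The outcome can cause its own absence. A girl who becomes pregnant and leaves before the next survey is no longer among the respondents to whom Table 1 assigns the questionnaire, and the article names no other source for her outcome. Choosing schools for high dropout among girls increases the exposure to this loss.

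A sample-size increase replaces numbers. It does not repair loss that depends on the outcome. Intention to treat fixes the arm in which a girl is analysed, but does not supply an outcome that was never collected.

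If pregnant girls leave equally often in both arms, the trial loses events and power. If they leave at different rates, the estimated effect is biased in either direction. A difference is conceivable because only the intervention schools have weekly on-site care and referral. The article offers no evidence on whether that would change who stays.

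**Working it through.** **The plan's own figures reproduce.** Inputs from Section 2.4.2: 29% and 19%, two-sided 5%, 80% power, intracluster correlation 0.01, cluster size 60.

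- Per arm before clustering: (1.96 + 0.842)² × (0.29×0.71 + 0.19×0.81) / 0.10² = 7.851 × 0.3598 / 0.01 = 282.5.
- Design effect: 1 + 59 × 0.01 = 1.59; 282.5 × 1.59 = 449 per arm, 898 in total.
- 898 × 1.10 = 988; 988 / 60 = 16.5, so 17, raised to 18 clusters, or 1080 girls (540 per arm).

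**Events against the loss allowance.** Expected pregnancies: 540×0.29 + 540×0.19 = 156.6 + 102.6 = 259. Ten per cent of 1080 is 108 girls. If all 108 were pregnant leavers, 108/259 = 42% of the events would be missing. That is an extreme case, but it shows that an unremarkable total can hide a large share of events.

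**Equal loss in both arms.** Let q be the share of pregnant girls whose pregnancy is never observed. The article gives no figure, so q is an assumption, shown over a range. No other girls are lost.

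Observed proportion = p(1−q) / [p(1−q) + (1−p)]

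At q = 0.5:
- 29% becomes 0.145 / (0.145 + 0.71) = 17.0%.
- 19% becomes 0.095 / (0.095 + 0.81) = 10.5%.

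Power uses the unpooled normal approximation, with the design effect at the reduced cluster size.

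| q (assumed) | Observed rates | Difference, points | Overall loss | Power |
|---|---|---|---|---|
| 0 | 29.0% vs 19.0% | 10.0 | 0% | 87% |
| 10% | 26.9% vs 17.4% | 9.4 | 2.4% | 84% |
| 25% | 23.5% vs 15.0% | 8.5 | 6% | 79% |
| 50% | 17.0% vs 10.5% | 6.5 | 12% | 65% |
| 75% | 9.3% vs 5.5% | 3.7 | 18% | 41% |

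**The same case on the odds-ratio scale.** Without loss: (0.29/0.71) / (0.19/0.81) = 1.74. At q = 0.5: (0.145/0.71) / (0.095/0.81) = 1.74. The factor (1−q) cancels, so equal loss does not bias the odds ratio. Its standard error grows because there are fewer events.

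**Loss that differs by arm, with no true effect (29% in both).** Assume 25% of pregnant girls are unobserved in control and 50% in intervention.
- Control: 0.2175 / (0.2175 + 0.71) = 23.5%.
- Intervention: 0.145 / (0.145 + 0.71) = 17.0%.
- False benefit: 6.5 points; false odds ratio, control to intervention, 0.75/0.50 = 1.5.
- Loss by arm: 0.29×0.25 = 7.25% and 0.29×0.50 = 14.5%, on average 10.9%.

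Swapping the two assumed shares gives a false harm of the same 6.5 points.

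**The case against.** The case against has several parts.

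- **The article does not exclude leavers.** A reader might infer from Table 1 that girls who leave are dropped from the trial, or that the two interviews are how the trial handles them. The text does not support either reading. The two girls are a qualitative stakeholder category, interviewed once. The in-school label may simply repeat the entry criterion. Twelve months of follow-up and intention to treat are promised. What stands is narrower: tool, respondents and school selection are fixed, and no route to a leaver's outcome accompanies them.
- **Not every event is lost.** Pregnancy may end schooling but need not, and a pregnancy reported at 6 months before leaving is captured. The dropout ranking covers all causes and is one of several selection criteria. This stands: the claim is a selective share of events, of unknown size.
- **Section 3 plans logistic regression, and equal loss leaves the odds ratio intact.** This stands as well. It does not protect precision, the absolute difference on which the trial is sized, or any estimate if loss differs by arm.
- **Very unequal loss would be visible.** One might infer that the effect could reverse while total loss still looks like the planned 10%. The plan's rates do not bear that out for a severe imbalance. With 70% of pregnant girls lost in control, 40% in intervention and 5% of other girls lost (all assumed), the observed rates are 11.4% and 12.9%, but loss is 23.9% against 11.7%. Such a gap would be noticed, though noticing it would not recover the outcomes.
- **Tracing procedures and missing-data analyses often sit in a full protocol or analysis plan.** This is fair for the details. It does not remove the tension among the features that the article itself fixes.

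**Conclusion.** The concern holds in a limited form. As written, the article ties a primary outcome to a questionnaire for girls in school, selects schools with high dropout among girls, acknowledges that pregnancy can end schooling, and offers only a flat 10% inflation against loss. A selective share of primary events is therefore at high risk of being missing, and intention to treat cannot be delivered for any girl whose outcome is not obtained.

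The size cannot be determined, because the article gives neither a dropout rate nor the part of it due to pregnancy. The 50% figure and the 25% versus 50% split are assumptions, and the 29% and 19% are taken as 12-month rates, as the sample-size section does. On those terms equal loss costs about 3.5 points of absolute difference and about 22 percentage points of power. Unequal loss can produce a difference of about 6.5 points where none exists. The stronger conclusion, that the plan discards its primary events, does not follow from the text.

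**What to change.** State that pregnancy status at 6 and 12 months is sought for every enrolled girl, whether or not she is still in school, by one identical procedure in both arms.

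- Take contact details at consent from all participants, including those aged 18 and 19, for whom Section 2.2 lists no parental consent.
- Use the girl's own report where possible. Use school leaving information only as a secondary source: Section 2.6 cites the dropout reports for rates, not for individual reasons.
- Do not rely on the senior woman teacher as informant. Section 2.8.1 has her supervising the intervention sessions, so her knowledge would differ by arm.
- Report loss by arm and reason.
- Add a sensitivity analysis that varies the pregnancy rate among missing girls separately by arm, including one version that counts pregnancy-related leavers as events.

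The cost is modest follow-up effort, one contact field and one added analysis. The downsides are that proxy information is less exact than self-report and that tracing must protect the girls' confidentiality. It has to be settled before follow-up begins, because analysis cannot recover outcomes that were not collected.
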